## Abstract

**Background:**

Cognitive problems associated with dementia affect a large proportion of older adults living in residential care. Knowledge of cognitive impairments is important for providing person-centred care (PCC). The impact of specific cognitive impairments on residents’ needs is often overlooked in dementia training and information about residents’ individual cognitive profiles are frequently underspecified in care-plans, potentially undermining the delivery of PCC. This can lead to reduced resident quality of life and increased distressed behaviours—a major cause of staff stress and burnout. The COG-D package was developed to fill this gap. Daisies provide a visual representation of a resident’s individual cognitive strengths and weaknesses in a colourful flower (Daisy) representing five cognitive domains. By viewing a resident’s Daisy, care-staff can flexibly adjust in-the-moment care-decisions and can consult Daisies in care-plans for longer-term planning. The primary aim of this study is to assess the feasibility of implementing the COG-D package in residential care homes for older adults.

**Methods/design:**

This 24-month feasibility cluster randomized controlled trial involves a 6-month intervention of the use of Cognitive Daisies in 8–10 residential care homes for older adults after training of care staff on the use of Cognitive Daisies in daily care (basic training) and on conducting the COG-D assessments with residents (advanced training). The key feasibility outcomes include % residents recruited, % COG-D assessments completed, and % staff completing the training. Candidate outcome measures for residents and staff will be obtained at baseline, and at 6 and 9 months post-randomization. COG-D assessments of residents will be repeated 6 months after the first assessment. A process evaluation will assess intervention implementation and barriers and facilitators to this through care-plan audits, interviews and focus groups with staff, residents, and relatives. Feasibility outcomes will be analysed against progression criteria to a full trial.

**Discussion:**

The results of this study will provide important information about the feasibility of using COG-D in care homes and will inform the design of a future large-scale cluster RCT to assess the effectiveness and cost-effectiveness of the COG-D intervention in care homes.

**Trial registration:**

This trial was registered on 28/09/2022 (ISRCTN15208844) and is currently open to recruitment.

## Background

Around 400,000 adults live in residential care [1], at least 70% have dementia [2] and of those 78% experience distress behaviours staff find challenging to support [3]. These have widespread impacts on resident and staff quality of life [4] and present significant financial costs to the NHS and social care [5]. Distress behaviours such as agitation, disinhibition, and aggression, cause significant suffering for the person with dementia, distress for those around them and burden and stress for care-staff. Their causes are multifactorial, including staff not always having adequate understanding of the impact of cognitive impairments on day-to-day functioning [6]. Cognitive impairments in dementia are complex as they vary as a function of dementia subtype [7] and premorbid cognitive status [8] and may fluctuate [9] and worsen with disease progression [10]. The importance of knowledge about a resident’s unique cognitive profile is acknowledged in best-practice models of Person-Centred Care (PCC) [11] and are considered core knowledge for social care-staff [12]. However, providing an in-depth understanding of the cognitive difficulties experienced in dementia is an area frequently overlooked in dementia training [13]. In practice, the available information about a resident’s cognitive problems is often underspecified (e.g., diagnosis only), not readily available to care-staff, incomplete or out of date [14]. Consequently, care-staff can have difficulty identifying needs that arise from specific cognitive problems and to adjust their care practices accordingly. This can lead to excess disability, seen in greater dependence in activities of daily living that a resident is potentially capable of.

The Cognitive Daisy (COG-D, Fig. 1) intervention [15] includes an assessment of cognitive abilities and provides a visual summary of the cognitive profile of a person with dementia to inform care-planning and practice. The COG-D visualizes a person’s cognitive strengths and limitations across five cognitive domains (visuo-spatial perception, comprehension, communication, memory, and attention) in the form of a Cognitive Daisy with 15 petals, each corresponding to one of the COG-D assessment areas. A coloured petal indicates that the person is likely to experience problems in this cognitive domain, whereas a white petal means they are not likely to show any difficulties in the corresponding area. The COG-D is not a diagnostic tool but assesses whether (as opposed to ‘how well’) a resident can perform a specific task (e.g., the ability to write a few words can be sufficient for effective communication of needs). The cut-off scores for coloured petals are based on normative data obtained from older adults living independently in the community who had no diagnosed cognitive impairments. COG-D assessment scores have high internal consistency and concordance with the 6-item cognitive impairment task [16] in normative data collected from healthy older adults [10].

**Fig. 1 Fig1:**
[figure not shown]
The Cognitive Daisy

The COG-D intervention package includes (1) staff training, consisting of (i) basic training for all care-staff on cognition in dementia and how Cognitive Daisies are used in daily practice, and (ii) advanced training for senior care-staff on conducting COG-D assessments; (2) completion of resident COG-D assessments and creation of individual Cognitive Daisies including specific care recommendations (6–8 common functional problems and suggested solutions automatically generated by a user-friendly application or via a printed ‘Petal-By-Petal Guide’). (3) Integration of COG-D in care-plans and display of the Daisies in useful locations (e.g., residents’ rooms). (4) Re-assessment if cognitive changes are noticeable in several domains, or on a 6-monthly basis.

In accordance with our Logic Model (see Fig. 2), implementation of the COG-D intervention is expected to (i) help care-staff to identify needs that arise from specific cognitive problems, (ii) enhance their understanding of how they could respond to these needs, (iii) provide practical approaches to meeting cognitive needs (iv) leading to a reduction in distress behaviours and improved quality of life for residents, increased sense of competence and reduced stress for care home staff and cost savings to the health and social care system.

**Fig. 2 Fig2:**
[figure not shown]
Logic model for the COG-D intervention

There is sparse literature on care home staff knowledge about cognition in dementia and interventions to support cognition-focussed assessment and care-planning, indicating that this is an area where there is a need for interventions to support the social care workforce. In development work in care homes, COG-D assessments were conducted for 33 residents across 6 care homes [10]. Care-staff (*n* = 27) rated the Daisies as improving their understanding of residents’ cognitive problems, found it easier to remember the specific problems of each resident and rated the Daisies as highly useful for delivery of PCC. Before the COG-D intervention can be rolled-out more widely, a more rigorous evaluation of the effectiveness and cost effectiveness of the intervention for residents is required. We first need to conduct a feasibility study to test some uncertainties about the study design, implementation in a larger number of care homes, and patient recruitment and retention. If the protocol for the study is feasible, the results will inform the design for a large-scale multi-centre, definitive cluster RCT, including choice of outcome measure, sample size, and strategies to respond to any identified barriers and facilitators of the study procedures, implementation, and training in care homes.

## Objectives

### Primary objective

To investigate the feasibility of conducting a future large-scale cluster RCT (cRCT) to assess the effectiveness and cost-effectiveness of the Cognitive Daisy (COG-D) intervention in care homes. Feasibility of a future cRCT will be investigated with regard to the following areas of uncertainty: (1) recruitment and retention of care homes, residents and care-staff in both intervention and control conditions, (2) adherence to COG-D intervention protocol, (3) acceptability and data completion rates of the candidate outcome measures, (4) estimates of effect sizes of proposed outcome measures to establish primary endpoint and sample size for the future CRT, (5) ability to collect health economic data required to undertake a cost-effectiveness analysis in the definitive trial.

### Secondary objectives

To investigate any signal of efficacy of the Cognitive Daisy (COG-D) on a range of outcome measures for residents and staff.To explore implementation and pathways of impact of the COG-D in care homes in a process evaluation.

### Trial design

A cluster-randomized controlled feasibility trial (cRCT) of usual care plus the Cognitive Daisy intervention (COG-D) compared to usual care (control), with two parallel arms and a 1:1 allocation ratio.

## Methods

### Study setting

Eight to 10 care homes for older adult care (on average 10–13 residents per care home) will be recruited in one region in the north-east of England from care home networks and organizations with whom the trial team have an existing relationship and who are not currently using COG-D. Selected care homes will vary in terms of type (residential/nursing) to include residents at different stages of dementia, and will not have been involved in the COG-D pilot study [10].

### Eligibility criteria (Table 1)

**Table 1 Tab1:** Eligibility criteria for care homes, care home residents, and care staff

Inclusion criteria:	Exclusion criteria:
*Care homes*	
• Residential or nursing home for older adults	• Have already used COG-D
• Provides care to people with dementia • Has minimum of 20 beds to facilitate recruitment of a sufficient number of residents in each care home	• Is subject to Care Quality Commission enforcement notices Local Authority quality concerns (to reduce care home burden) • Is involved in another complex intervention trial at the time of recruitment
*Residents—all*	
• Consenting to take part (personal or via consultee)	• Receiving end of life care
*Residents—taking part in COG-D assessment*	
• Can communicate well enough in English to not require an interpreter	
• Vision/hearing (with correction) adequate to participate in COG-D assessment	
• Deemed well enough by staff/researcher to complete the assessment by a member of staff or the assessor	
*Care home staff*	
• Permanent, contracted, agency, or bank member of staff at time of data collection	• Acting as a nominated consultee for any residents participating in the trial
• Provide informed consent	
• Have sufficient proficiency in English to contribute to the data collection required for the research	

### COG-D intervention

The COG-D intervention will be commenced in all intervention arm care homes immediately post-randomization and consists of the following two phases: Phase 1: staff training and COG-D assessments of residents’ abilities, phase 2: COG-D use in daily practice (6 months) and COG-D re-assessment of residents’ abilities.

#### Phase 1

##### Staff training

Basic COG-D Staff Training (~ 45 min): aimed at all care-staff who will use the Cognitive Daisy in daily care. The training introduces the Cognitive Daisy, describes the five cognitive domains represented in the coloured petals and the different functions association with each petal with reference to the Petal-By-Petal guide. To accommodate care home preferences and the importance of flexibility in terms of mode of delivery (e.g., temporary care home closure), this training can be completed either individually (online), in groups of staff from single or multiple care homes using videoconferencing, or in single care home groups face-to-face. This feasibility study will explore the use of these different modes of delivery and the reasons thereof.

Advanced COG-D Staff Training (~ 3 h): aimed at senior staff who will be involved in the COG-D assessment of residents. This practice-based training introduces staff to the COG-D assessment process, the individual assessment items, how to create Daisies and how to use the Daisies and the Petal-By-Petal guide to update a resident’s care-plan. This training can be completed in groups of staff from single or multiple care homes, either in person or in videoconferencing sessions.

##### COG-D assessments of residents

The COG-D assessments will be completed by a researcher and shadowed by senior staff who completed the Advanced COG-D Staff Training. The assessment tool COG-DAA constitutes 16 tasks, variants of which are routinely used for assessment of dementia and other neurological disorders. Assessments are conducted using the assessment booklet (A6 size), which allows assessment in a comfortable environment. A detailed COG-D assessment script is used with verbatim instructions for each test. The order of the tests allows for breaks without affecting performance. The test will be introduced as ‘puzzles’ or ‘activities’ to reduce any negative associations or performance anxiety. All materials are presented in a large font and line drawings are avoided (for instance, photographs of real objects are used for object naming and object recognition). A version for non-verbal responses is included to accommodate people with problems with speech production (COG-D SSP). Word lists for the different tests were carefully balanced in terms of age of acquisition, word-length, word-frequency, semantic category, and concreteness [15].

If the score for a test is below the cut-off score, the petal associated with the specific test is coloured. If the test cannot be completed, the petal will be grey. Daisies can be created in different ways to accommodate different uses. Assessors can choose to use a sticker system to create the Daisy together with the resident, or to create a digital version (using a web-based application) for inclusion in care plans (or both). For both methods, the Daisies can be produced without labels (for display) or with labels (e.g., for care plans). The digital version includes the pages of the Petal-By-Petal guide for the coloured petals. The study will explore how the different methods are used in the care homes.

COG-D re-assessment is conditional for the usefulness of COG-D. A full re-assessment is recommended if cognitive changes are noticeable in several domains or following a significant change in a resident’s health status. Individual skills can be re-assessed if changes are observed for specific cognitive abilities. Social context or time-of-day fluctuations in performance may occur; re-assessment of an individual test is recommended if the result deviates consistently from observations of care-staff or family/relatives. In the present study, COG-D re-assessment is only conducted after the COG-D use in Daily Practice intervention period.

#### Phase 2

##### Use of COG-D in daily care practice

The Daisies without labels will be placed in locations where they are most useful (e.g., in residents’ rooms) and Daisies with labels are included in the care-plans. Recruited staff will be provided with the Petal-By-Petal Guide. Larger posters of the Cognitive Daisy (not resident-specific version) will be displayed in dining areas and in communal spaces where scheduled activities take place.

To support staff and to monitor use of resident Daisies, a range of activities will be arranged during this phase of the intervention: (1) weekly guided ‘huddles’ [17] and fortnightly virtual COG-D drop-in sessions for staff to ask questions about the use of Cognitive Daisies, share good practice and to monitor use; (2) care plan review meetings (after the initial and the second COG-D assessment period) to discuss how Daisies can be used to update care-plans; (3) monthly COG-D Assessor drop-in sessions (senior staff) to ask questions and for sharing of good practice; (4) monthly newsletters to update intervention arm care homes about the progress of the COG-D project and to summarize suggestions on the use of COG-D in practice, based on the huddle and drop-in session discussions. Control homes will receive the newsletter content related to general study progress without any COG-D specific content.

##### COG-D re-assessment of residents

Six months after the first COG-D assessment, residents will be re-assessed on COG-D by researchers and senior staff. Senior staff will be encouraged to lead the assessments and both assessors will score performance independently for concordance rates.

### Intervention fidelity and adherence

Fidelity of the intervention will be optimized by using the same researchers for providing the Advanced Training in all intervention care homes and the same training materials for face-to-face and online training sessions for the Basic Training. COG-D assessors use a detailed COG-D assessment script with verbatim instructions for each test and detailed scoring instructions are provided. If COG-D re-assessments are led by senior staff, scoring is conducted independently by both assessors to ensure consistency. Fidelity and adherence will be monitored during the huddles and drop-in sessions where staff can ask questions and share good practice under supervision of the researchers. Fidelity and adherence will further be explored during the focus groups with staff during the process evaluation phase to inform the staff training and monitoring processes for the future trial.

### Usual care

Usual care is defined as normal care delivered within the setting, which will continue in both arms. No restrictions will be imposed on current practices or on homes undertaking additional development or training as part of usual care, except for control arm homes being required not to implement COG-D during their trial involvement period.

### Outcomes

Primary outcome of this study are the feasibility outcomes, including recruitment and retention rate, acceptability, fidelity and adherence to COG-D intervention protocol, acceptability and data completion rates, and feasibility of health economic assessment. Key feasibility criteria a presented in Table 2. Secondary outcomes are the candidate outcomes for a definitive cRCT (see Table 3).

**Table 2 Tab2:** Key progression criteria

*Key progression criteria*	
Percentage recruited residents	*Green > 60%, amber 40–60%, red < 40%*
Percentage of recruited residents for completion of COG-D and COG-D re-assessment	*Green > 60%, amber 40–60%, red < 39; re-assessment: 70% of these estimates*
Percentage of recruited staff completing basic training	*Green > 60%, amber: 40–60%, red < 40%*
Percentage of recruited senior staff completing advanced training	*Green > 75%, amber 60–74%, red < 60%*

**Table 3 Tab3:** Candidate outcome measures

Outcome measures	Outcome	Description
*Residents*		
Cohen-Mansfield Agitation Inventory CMAI [23, 24]	Agitation	Lists 29 agitated behaviors. By proxy rating of frequency of occurrence in the previous 2 weeks, ranging from never (1) to several times an hour (7). Scores range from 29 to 203. A high score indicates high levels of agitation.
Quality of Life in late-stage Dementia scale QUALID [25]	Quality of Life	By proxy ratings (1 to 5) of 11 behaviors. Scores range from 11 to 55; low scores indicate higher levels of quality of life.
Bristol Activities of Daily Living Scale BADLS [26]	Independence in daily activities	By proxy rating (1–5) of average ability on 20 activities in the preceding 2 weeks. Scores range from 20 to 100. Low scores indicate higher levels of independence.
EQ-5D-5L: Instrument to describe and value health [27]	Health-related quality of life	By proxy rating (1–5) of health-related quality of life in five domains. Scores range from 20 to 100. A low score indicate a higher level of health-related quality of life.
Functional Assessment Staging of Alzheimer’s disease FAST [20]	Estimate of dementia stage	Functional scale designed to evaluate people at the more moderate-severe stages of dementia. The scale has seven stages, the highest rating (7) indicates ‘severe dementia’. Ratings are guided by functional milestones.
*Staff*		
Sense of Competence in Dementia Care Scale SCIDS [28]	Perceived competence of own delivery of dementia care.	Seventeen statements require a response (varying from ‘not at all’ (1) to ‘very much’ (4)) with reference to the questions ‘how well do you feel you can…’. Scores vary from 17 to 68. A high score indicates a higher level of sense of competence.
Copenhagen Burn-out Inventory CBI [29]	Burn-out	19 Items refer to personal burnout, work-related-burnout and client-related burnout. Scores are averaged over the number of questions for each category. Higher scores indicate higher levels of burn-out.
Cognitive Daisy Questionnaire COG-D Q [15]	Perceived relevance of knowledge about cognitive strengths or weaknesses	Non-validated mixed 3-item scale (open-ended and rating (1–5) items). Each item is analysed separately.

### Participant timeline

Care home and individual participant timelines are set out in the study flow-diagram (see Fig. 3):

**Fig. 3 Fig3:**
[figure not shown]
Study flow chart

### Sample size

In line with recommended sample sizes for feasibility studies [18], the aim is to recruit 70 care home residents (35 per arm). To accommodate 30% loss to follow up, 100 residents will be recruited. This sample size will allow for reliable estimation of key feasibility figures, e.g., the 95% confidence interval on retention rate will have the width of ± 9%. To ensure that the target recruitment rate of residents can be achieved from 8 to 10 care homes (it is expected that on average ~ 40–60% of residents will be recruited), only care homes with a minimum of 20 beds will be considered eligible (no maximum limit will be used). We aim to recruit 50 members of staff and will report on the feasibility of recruiting staff for the COG-D intervention.

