### Assignment of intervention

Randomization of care homes will take place after collection of baseline measures. A web-based randomization system built in the REDCap Cloud electronic data capture system (EDC) will be provided by the Hull Health Trials Unit (HHTU). Randomization by minimization will be undertaken at care home level in 1:1 ratio and stratified by site size (large > 40 beds–small < 40 beds). Each care home will be randomized centrally and dynamically after collection of baseline data is completed. A separate randomization strategy SOP with details on randomization by minimization will be produced and implemented.

To prevent experimenter bias during collection of post-intervention candidate outcome measures (6 and 9 months post-randomization), one of the three trial-specific researchers will be blinded for the condition of each care home (UC or UC + COG-D). Care homes allocated to the COG-D intervention arm will be reminded to remove any references to COG-D (e.g., posters, leaflets, Daisies) in areas where researchers meet care staff who provide proxy data for residents at 6 and 9 months post-randomization. If unblinding happens by accident, then this will be reported to the CI. The feasibility and effectiveness of this approach will be considered in the design of the future planned RCT.

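### The ±9% precision given for retention treats 100 residents from 8–10 randomised homes as independent, and it does not carry over to figures measured only in the intervention arm

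*Protocol article*

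**What the plan says.** The Sample size section starts from published recommendations for feasibility studies: "the aim is to recruit 70 care home residents (35 per arm"). It then allows for attrition: "To accommodate 30% loss to follow up, 100 residents will be recruited". The precision statement follows, with ±9% as its value: "This sample size will allow for reliable estimation of key feasibility figures, e.g., the 95% confidence interval on retention rate will have the width of" that amount. It is offered as an example of reliable estimation of the study's main feasibility figures. The section mentions no ICC or design effect.

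The design is clustered. Study setting says "Eight to 10 care homes for older adult care (on average 10–13 residents per care home) will be recruited", and Assignment of intervention says "Randomization by minimization will be undertaken at care home level in 1:1 ratio". The Withdrawal section allows a whole home to leave, as well as an individual. ICCs appear only under Data analysis, as quantities to be estimated for the candidate outcomes of the future trial.

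On delivery, the COG-D intervention section says "The COG-D intervention will be commenced in all intervention arm care homes immediately post-randomization", and the resident assessments are part of that intervention. Table 2 sets the progression colours for COG-D completion, with amber at 40–60% and scaled limits for re-assessment. The primary objective asks for recruitment and retention in both conditions.

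**The concern.** Residents of one home share its management, staffing, closures and decision to stay in the study, so their retention is unlikely to be independent. If one home stopped data collection, it would remove 10 to 12.5 of the 100 residents at once. At 70% retention, 7 to 8.75 of these would otherwise have been kept, which is nearly the whole stated half-width.

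The sentence also goes beyond retention. A reader will take ±9% as a guide to how well the other feasibility percentages will be known. COG-D completion and re-assessment exist in only one arm, so they rest on about half the residents and half the homes. These percentages are compared with progression bands, so overstated precision makes a colour look firmer than the data can make it.

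**Working it through.** **Inputs from the protocol article.** N = 100 residents; 30% loss, so retention p = 0.70; 8–10 homes, so m = 100/8 = 12.5 or 100/10 = 10 residents per home; 1:1 allocation of homes, so about 50 residents in 4–5 homes per arm; amber band 40–60% for COG-D completion.

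**Assumption.** No ICC for retention or completion is given. I use 0.02–0.05 as the main range and show 0.01 and 0.10 for pooled retention. Home sizes are taken as equal; unequal sizes would widen the intervals further.

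**1. Reproduce the plan's figures.** 70/(1−0.30) = 100. Half-width = 1.96×sqrt(0.7×0.3/100) = 8.98%, so ±9% is reproduced. The obvious alternatives do not give it: n = 70 gives ±10.7%, and p = 0.5 with n = 100 gives ±9.8%. The stated figure is therefore the formula for 100 independent residents, both arms pooled.

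**2. Allow for clustering in pooled retention.** Half-width = c×sqrt(0.21/100×DE), with DE = 1+(m−1)×ICC. Here c is 1.96, or t on homes−1 degrees of freedom (2.262 for 10 homes, 2.365 for 8).

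| ICC | DE, 10 / 8 homes | z, 10 / 8 homes | t, 10 / 8 homes |
|---|---|---|---|
| 0.01 | 1.09 / 1.115 | ±9.4 / ±9.5% | ±10.8 / ±11.4% |
| 0.02 | 1.18 / 1.23 | ±9.8 / ±10.0% | ±11.3 / ±12.0% |
| 0.05 | 1.45 / 1.575 | ±10.8 / ±11.3% | ±12.5 / ±13.6% |
| 0.10 | 1.90 / 2.15 | ±12.4 / ±13.2% | ±14.3 / ±15.9% |

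With z, the half-width reaches 9.5% at an ICC of about 0.010 (8 homes) to 0.013 (10 homes), and 10% at about 0.021 to 0.027.

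**3. Intervention arm only, n = 50.** Before any clustering:
- 70%: 1.96×sqrt(0.21/50) = ±12.7%
- 60%: 1.96×sqrt(0.24/50) = ±13.6%
- 50%: 1.96×sqrt(0.25/50) = ±13.9%

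For 60% completion with the same design effects, and t on 4 or 3 degrees of freedom (2.776 or 3.182):

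| ICC | z, 5 / 4 homes | t, 5 / 4 homes |
|---|---|---|
| 0.02 | ±14.8 / ±15.1% | ±20.9 / ±24.5% |
| 0.05 | ±16.4 / ±17.0% | ±23.2 / ±27.7% |

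**4. Set against the amber band.** With 100 independent residents, an observed 50% has ±9.8%, or 40.2% to 59.8%, just inside amber. With 50 residents and no clustering it is 36.1% to 63.9%, already crossing both limits. At ICC 0.05 the z half-width is ±16.7% (5 homes) to ±17.4% (4 homes).

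**5. Staff training.** The article aims for 50 staff and does not say how they divide between arms. At 60% completion before clustering, the half-width is ±13.6% if all 50 are in intervention homes and 1.96×sqrt(0.24/25) = ±19.2% if they split evenly. Either figure depends on that split.

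**The case against.** The strongest reply is that the calculation is correct for what it computes, that no ICC for retention is known, and that the loss is small if the ICC is low. This stands in part. At ICC 0.01–0.02 the pooled z-based half-width is ±9.4–10.0%, at most one point from the stated figure. The documents do not show how far deaths and transfers cluster by home. What can be said firmly is that clustering was left out; the size of the shortfall rests on an assumption.

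Some stronger readings should be set aside:

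- A reader might infer that ±9% is the only basis for the sample size. It is not. The 70 residents come from cited recommendations and the 100 from the attrition allowance, so correcting ±9% changes neither.
- A reader might infer that retention is really known only to ±14–20%. At the assumed ICC of 0.02–0.05, pooled retention is ±9.8–13.6% across both methods. The larger values belong to arm-only or staff percentages, for which the article states no precision of its own.
- A reader might infer that ±9% drives a progression colour. Retention is not a row of Table 2. The percentage of residents recruited also has a larger denominator: at the expected 40–60% uptake, 100 recruits imply about 167 to 250 residents.

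It can also be said that the way intervals are calculated belongs in an analysis plan that is not shown. That is fair for the reporting method. It does not cover a precision figure that the article itself prints and offers as typical of its main feasibility results.

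**Conclusion.** The concern holds as worded in the heading. The ±9% is a correct calculation applied to the wrong design: it needs an ICC of essentially zero, in a trial that randomises 8–10 homes and provides for whole-home withdrawal. The pooled shortfall is about one to two points with z, or two to five with t, at an assumed ICC of 0.02–0.05.

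The intervention-arm part is the more consequential and needs no ICC. About 50 residents give ±13.6% at 60% even if independent, and an observed 50% then overlaps both red and green. It assumes an even split of residents between arms and that all recruited intervention-arm residents form the denominator; a smaller denominator would widen the interval. The size of the trial is not called into question.

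**What to change.** Replace the ±9% statement with precision figures that name the assumed ICC range and the number of homes, given separately for pooled and intervention-arm percentages and using one method throughout. For 8–10 homes and ICC 0.02–0.05:

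- **With t on homes−1:** about ±11–14% for pooled retention of 70%, and about ±21–28% for 60% COG-D completion in the intervention arm.
- **With z:** about ±10–11% and ±15–17% respectively. This is simpler but optimistic with so few homes.

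The t-based pair is preferable; the two methods should not be mixed in one sentence. Any precision quoted for staff training should state the assumed split of the 50 staff between arms.

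Report the feasibility proportions with cluster-adjusted intervals beside the progression colours, so that a colour whose interval crosses a limit is seen as uncertain. The cost is a sentence or two and a less favourable stated precision. No added recruitment is required.
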